### Participants

Patients (n = 60) diagnosed with insomnia will be recruited through referrals from health care professionals at Kingston Health Sciences Centre (Kingston, Canada), family physicians, and other health care providers or self-referrals in Kingston, Ontario, Canada. Patients who show interest in the study will then be advised to meet with a study research coordinator who will provide them with letters of information containing study details. If patients wish to participate, written and verbal consent is required for participation and will be collected by the research coordinator.

After consenting to participate in the study, a mini-international neuropsychiatric interview (MINI) based on the Diagnostic and Statistical Manual of Mental Disorders, Fifth Edition (DSM-5) will be completed by a psychiatrist on the research team to confirm diagnosis and eligibility [42]. Inclusion criteria include the following: at least 18 years of age at the start of the study, non-organic insomnia (insomnia not due to other psychiatric disorders, or medical conditions); the presence of insomnia symptoms for at least 3-month; difficulty initiating and/or maintaining sleep for ≥ 30 minutes; ability to speak and read English; consistent and reliable access to the internet; and not using or changing the dose of sleep medications within the six weeks before commencing the study [43]. Patients diagnosed with insomnia of all severities according to DSM-5 will be included in this study. Exclusion criteria include the presence of another untreated sleep disorder requiring other treatments such as sleep apnea or alcohol, or substance use disorder, ongoing CBT, and non-assessed or untreated somatic symptom disorder according to the DSM-5. Pregnant women or participants who may become pregnant will be excluded from participation owing to concerns about potential adverse fetal effects from trazodone.

### Blinding, randomization and treatment allocation

An independent researcher will conduct participant randomization using the MS Excel randomization function with a 1:1 ratio. This will determine whether participants are assigned to the e-CBTi or the pharmacotherapy group. Blinding of participants and therapists directly involved in patient care is not possible due to the nature of this study. However, all people involved in outcome assessments and data analysis will be blinded from the group assignment.

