### Sample size

A priori power analyses using the G*Power V3.1 software indicated that a sample size of 36 participants would provide adequate power to detect a medium (f = 0.25) group x time interaction effect using repeated measures analysis of variance (ANOVA) with four sequential measurements per subject per week when the correlation among the measures was 0.3 (α = 0.05). Given the likelihood of participant dropout or withdrawal, participants have been purposely over-sampled to obtain meaningful and statistically significant results regarding changes in their symptoms at the end of the study. Based on previous experience with e-CBTi in similar patient populations, a dropout of up to 25% is anticipated [38]. Considering that former studies of similar nature have suggested that N = 20, 30, 24 per study arm has produced statistically significant interaction effects [39–41]. A sample size of 30 participants in each arm or 60 participants in total, is planned to be recruited for this study to detect significant results with p = 0.05 after expected attrition.

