## Results

The study was reviewed for ethical compliance and ethics approval was received from the Queen’s University Health Science and Affiliated Teaching Hospitals Research Ethics Board in October 2021. Participant recruitment began in November 2021. Recruitment has been conducted through social media advertisements, physical advertisements, and physician referrals. To date, 18 participants have been recruited (e-CBTi: n = 11; trazodone: n = 7). Data collection is expected to conclude by December 2022, and data analyses are expected to be completed by January 2023 with analysis of variance (ANOVA) for continuous outcomes (e.g., ISI score, sleep diary, Fitbit), and chi-square tests for categorical outcomes (e.g., sex, ethnicity, employment status). Any modifications to the study will be submitted as amendments. The study results will be published in peer reviewed journals and a lay summary will be sent to interested participants.

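### Baseline ISI balance is left to chance in a 60-patient, all-severity trial, and the stated pre-to-post interaction test over-corrects a chance imbalance and loses precision compared with adjusting for baseline ISI

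*Protocol article*

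**What the plan says.** All references are to the protocol article.

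- **Allocation** (Blinding, randomization and treatment allocation): an independent researcher allocates patients "using the MS Excel randomization function with a 1:1 ratio". No block, stratum or minimisation factor is named, and the text does not say that the draw is unrestricted.
- **Population** (Participants): "Patients diagnosed with insomnia of all severities according to DSM-5 will be included".
- **Size** (Sample size): "A sample size of 30 participants in each arm or 60 participants in total". The power calculation is for a group-by-time interaction with f = 0.25, four measurements, a correlation of 0.3 and α = 0.05. It gives a total of 36, and dropout of up to 25% is expected.
- **Primary outcome** (Primary outcome; Outcome evaluation): ISI, collected at week 0, weekly, and after treatment.
- **Analysis** (Statistical analyses): two-way repeated-measures ANOVA and multilevel regression, with group and time (pre- to post-treatment) as main effects and their interaction as the treatment comparison. No baseline ISI covariate is in the stated model.
- **Progress** (Results): "18 participants have been recruited (e-CBTi: n = 11; trazodone: n = 7").

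**The concern.** With about 30 patients per arm drawn from the whole severity range, the arms can differ noticeably in mean baseline ISI by luck alone. How much that matters depends on the analysis. The stated model gives each arm its own pre-treatment mean, so for two time points the interaction is the difference between arms in change from baseline. Change from baseline subtracts the whole baseline difference. When the pre-post correlation is well below 1, only part of that difference would have persisted to the end of treatment. The arm that starts worse therefore appears to improve more, even if the treatments are equally effective.

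At stake are the credibility of the primary estimate if the arms start apart, and precision that a small trial could recover from data it already collects.

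**Working it through.** **Inputs.** From Sample size: 30 per arm, ρ = 0.3, f = 0.25, four measurements, total 36, 25% dropout. From Results: 11 and 7 of 18. Assumed: equal ISI variance σ² in both arms and at both times, an approximately normal baseline mean difference, and a single pre-post contrast.

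**1. The plan's own figure.** For the within-between interaction, λ = f²·N·m/(1−ρ) = 0.0625 × 36 × 4/0.7 = 12.9, on 3 and 102 degrees of freedom. Power is 85.2%. The article says only that power is adequate, so 36 is compatible with its inputs but cannot be confirmed. Dropout inflation gives 36/0.75 = 48, and 60 leaves 60 × 0.75 = 45. The input carried forward is ρ = 0.3.

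**2. Size of a chance baseline difference.**
- At 30:30, SE = σ√(1/30 + 1/30) = 0.258σ. The 95% range is ±0.51σ.
- P(|difference| > 0.25σ) = P(|Z| > 0.25/0.258) = 33%.
- At 34:26 the SE is 0.261σ, so unequal arms hardly change this.
- With 45 patients left, the SE is about 0.30σ and the probability about 40%.

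**3. Effect on the change contrast.** Given a baseline difference D and no treatment effect, the expected difference in change is (ρ − 1)D. With ρ = 0.3 and D = 0.25σ this is −0.7 × 0.25σ = −0.175σ, or about 0.18 SD. Comparing post scores with no use of baseline would be shifted by ρD = 0.075σ. At this correlation, then, subtracting baseline does more harm than ignoring it. With baseline as a linear covariate, the expected shift is zero.

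In ISI points, if the SD is 4 to 6 (an assumption; the article gives none), D = 0.25 SD is 1.0 to 1.5 points and the shift is 0.7 to 1.05 points.

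**4. Precision.** Variance per patient, in units of σ²:

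| Contrast | Formula | ρ = 0.3 | ρ = 0.5 | ρ = 0.7 |
|---|---|---|---|---|
| Change from baseline | 2(1−ρ) | 1.40 | 1.00 | 0.60 |
| Baseline-adjusted | 1−ρ² | 0.91 | 0.75 | 0.51 |
| Reduction | 1 − (1+ρ)/2 | 35% | 25% | 15% |
| Shift for D = 0.25σ | (1−ρ) × 0.25σ | 0.175σ | 0.125σ | 0.075σ |

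Only 0.3 comes from the article; 0.5 and 0.7 show the range. At 30:30 and ρ = 0.3 the SE falls from √(1.4 × 2/30) = 0.306σ to √(0.91 × 2/30) = 0.246σ. The gap 2(1−ρ) − (1−ρ²) equals (1−ρ)², which is never negative, so adjustment does not lose at any correlation, apart from one degree of freedom.

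**5. What 11:7 shows about the list.**
- The probability of an 11:7 split in either direction among 18 is 24.3% under coin-flip allocation (2 × 31,824/262,144) and 24.0% under a shuffled list of 30 and 30.
- Unstratified fixed blocks of 2, 4, 6, 8 or 10 cannot give a difference of 4 at patient 18. Larger blocks such as 12 or 14 can, and stratified blocks are not excluded.
- If allocation is a coin flip, the chance of finishing at exactly 30:30 from 11:7 is C(42,19)/2⁴² = 10.2%.

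**6. Cost of unequal arms.** A two-sample test with 80.0% power at 30:30 has 79.3% at 34:26 and 78.4% at 36:24. Averaged over coin-flip allocation of 60 it has 79.4%.

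**The case against.** Randomisation balances severity in expectation, and the standard error of the change contrast already includes chance imbalance (1.4 = 0.91 + 0.7²). The planned test therefore keeps its error rate. This stands: the point concerns efficiency and the reading of the realised estimate, not validity.

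Pre-treatment ISI is already in the model as a level of time. That is true, but it enters with a fixed coefficient of 1 where the protocol's correlation implies 0.3, and this is the source of the over-correction.

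Covariates are often left to the analysis plan, and a journal article condenses. That would answer a complaint of omission. The article does, however, state the primary model, and the point is that the stated model can be bettered. Baseline need not be a strong predictor for this to hold: at ρ = 0.3 it explains only 9% of outcome variance, and the gain comes mainly from not subtracting it in full.

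A reader might go further and infer from 11:7 that allocation is unrestricted and will miss 30 per arm. The documents do not support this. The count fits a shuffled 30/30 list, which would deliver exactly 30:30, as well as it fits a coin flip, and list construction is a detail an article may omit. Nor is an arm falling below 18 after dropout a failure against the 36 required, because 36 is a total. At 37:23 with 25% loss the balanced equivalent is 4 × 27.75 × 17.25/45 = 42.6.

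**Conclusion.** The point holds as one about the primary analysis. Balance of baseline ISI is left to chance, with a 33% probability of a difference above 0.25 SD at 30:30. The stated interaction test turns a 0.25 SD difference into a shift of about 0.18 SD. It also has variance 1.4σ² where 0.91σ² is available.

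These sizes rest on the article's correlation of 0.3, equal variances, and a single pre-post contrast. With higher correlations the shift and the loss shrink but keep their direction (0.075 SD and 15% at 0.7). An interaction over several weekly scores would give different figures, though it still estimates the arms' baseline means separately.

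It would be wrong to conclude that severity is unbalanced, that the test is invalid, or that the trial will not reach 30 per arm. Unequal arms would cost well under one point of power on average and 1.6 points at 36:24.

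**What to change.** Make the primary analysis a comparison of post-treatment ISI between arms with continuous baseline ISI as a covariate. Alternatively, use the post-baseline weekly ISI scores as outcomes in the multilevel model already planned, again with baseline ISI as a covariate. Fix the change before anyone sees outcome data by arm. It costs a short amendment and one degree of freedom, with no new data and no more patients on this account.

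Separately, state how the Excel list was built. If it proves unrestricted, the sponsor could consider concealed blocks of varying size, stratified on ISI, for the remaining 60 − 18 = 42 participants. This is a trade-off, and the fix above does not depend on it:

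- Balanced blocks would add 21 to each arm and finish near 32:28, not 30:30.
- Blocks add some predictability in an open-label, single-site trial.
- If the present list is a shuffled 30/30, replacing it would give up exact balance.
- The Procedure section describes the week-0 questionnaires after allocation, so stratifying would need an ISI score taken before randomisation. The timing of the baseline ISI is worth stating for the covariate as well.

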### Procedure

Upon completion of the initial assessment and treatment allocation, all eligible participants will be added to a secure online platform, OPTT. The OPTT system is designed by the lead author, and developed in collaboration with a team of physicians, and web developers with expertise in online CBT, neuroscience, and data. The user can operate the OPTT system on any electronic devices connected to Wi-Fi. All e-CBTi sessions and therapist-participant interactions during the study period will occur over this platform. The same set of therapists of the same orientation, training, shared environment, and supervision is used between groups to control for the potential covariates impacting the therapeutic relationship and minimize the potential of the therapist’s effects on patient outcomes. At baseline (week 0), all participants will complete a demographic survey, and clinically validated sleep questionnaires. Online questionnaires will also be completed weekly during the study period, and post-intervention (week 7–8). Participants assigned to the psychotherapy group will receive e-CBTi along with their treatment as usual (TAU) for seven weeks. TAU is defined as the standard psychiatric or pharmaceutical treatment for patients’ conditions with no restrictions apart from the use of the experimental treatment (trazodone and CBT). If TAU includes a medication that could affect sleep, the dosage must remain consistent 6 weeks prior to the study and during the study period. Participants assigned to the pharmacotherapy group will be prescribed trazodone in the first session in addition to TAU. Once post-test questionnaires are complete, participants allocated to the pharmacotherapy group will also have the opportunity to participate in the therapist-guided e-CBTi program after the study period.

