### Outcome evaluation

All participants are expected to wear the Fitbit sleep tracking device during the study duration and complete the Insomnia Severity Index (ISI) questionnaire and sleep diary on the OPTT platform at baseline (week 0), weekly during the study, and post-treatment (week 7–8). A tutorial for using the sleep diary on the platform will be provided to all participants. An independent researcher will collect all quantitative and qualitative measures by extrapolating recorded information through the OPTT platform.

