### Primary outcome

*Insomnia Severity Index (ISI)* The primary outcome measure will be ISI [44]. ISI is a valid, reliable, and sensitive global index of self-reported insomnia symptoms that contains seven questions rated from 0 to 4 on the severity of insomnia problems, sleep satisfaction, interference of insomnia with daytime functioning; noticeability of sleep problems by others; and distress about sleep difficulties. Psychometric parameters of ISI are adequate, sensitive to change, and have been validated for online use [45].

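### As written, the baseline of the self-rated primary outcome is collected after allocation, from unblinded participants who may already know their arm

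*Protocol article*

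**What the plan says.** Four parts of the protocol article bear on the order of events.

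- **Before allocation.** The Participants section describes consent and then a MINI diagnostic interview, which "will be completed by a psychiatrist on the research team to confirm diagnosis and eligibility". It mentions no ISI or diary at this stage.
- **Allocation and platform access.** The Procedure section states: "Upon completion of the initial assessment and treatment allocation, all eligible participants will be added to a secure online platform, OPTT". Later in the same paragraph: "At baseline (week 0), all participants will complete a demographic survey, and clinically validated sleep questionnaires".
- **Where the baseline is recorded.** Under Outcome evaluation, all participants are to "complete the Insomnia Severity Index (ISI) questionnaire and sleep diary on the OPTT platform at baseline (week 0), weekly during the study", and again after treatment.
- **Blinding and outcome.** "Blinding of participants and therapists directly involved in patient care is not possible due to the nature of this study". Under Primary outcome, "The primary outcome measure will be ISI", and the instrument is described there as self-reported.

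The Statistical analyses section tests the group x time interaction on ISI, diary and Fitbit measures, to compare change from pre-treatment to post-treatment. Missing data are not imputed.

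**The concern.** In an open-label trial with a self-rated outcome, a baseline recorded before the arm is known cannot be affected by it. A baseline recorded afterwards can. A participant pleased or disappointed with the assignment may rate the past weeks' sleep differently, and the direction may differ by arm. The Introduction itself cites a three-fold patient preference for psychological over drug treatment across psychiatric disorders. That makes arm-dependent reactions plausible, although it says nothing about ISI reporting.

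Because the treatment effect is read from change since baseline, a shift present at week 0 and gone by the end of treatment appears as a difference in change. The analysis cannot separate it from a treatment effect. The blinded outcome assessment that the article promises gives no protection, since the participant is the rater.

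The order has a second consequence. Anyone who leaves between allocation and week 0 has no baseline ISI and, with no imputation, cannot contribute to the change comparison, although the article says data from all participants will be included.

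**Working it through.** **Order of events.** Procedure: initial assessment and allocation come first, then access to OPTT. Outcome evaluation: the week-0 ISI and diary are completed on OPTT. Anything completed on OPTT therefore follows allocation. The only assessment described before allocation is the MINI, and no available text places an ISI or diary entry earlier.

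**Size of the possible bias.** The article gives no figure for a baseline shift, so this is an illustration over an assumed range.

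Inputs:
- 60 planned, up to 25% dropout (Sample size): 60 x 0.75 = 45 completers, or 22.5 per arm.
- Correlation among measures r = 0.3, two-sided alpha 0.05 (Sample size).
- Assumed difference d between arms in baseline reporting, absent at the end of treatment: 0.1, 0.25 and 0.5 SD.

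The article's planning figure reproduces with these inputs. N = 36, four measures, f = 0.25 and r = 0.3 give noncentrality 36 x 4 x 0.0625 / 0.7 = 12.86 and power 0.852. The present point does not depend on that figure.

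*Comparison of pre-to-post change (two timepoints, SD units).* With no true treatment difference, the bias equals d in absolute size.

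SE = sqrt(2(1 - r) x 2/n) = sqrt(1.4 x 2/22.5) = 0.353

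The type I error is the two-sided rejection probability of a noncentral t with 43 degrees of freedom and noncentrality d/SE.

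*Comparison adjusted for the same baseline as a covariate.* The bias becomes r x d.

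SE = sqrt((1 - r^2) x 2/n) = sqrt(0.91 x 2/22.5) = 0.284

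| Assumed d (SD) | d/SE, change | Type I error, change | Bias after adjustment (SD) | Type I error, adjusted |
|---|---|---|---|---|
| 0.1 | 0.28 | 5.9% | 0.03 | 5.1% |
| 0.25 | 0.71 | 10.7% | 0.075 | 5.8% |
| 0.5 | 1.42 | 28.3% | 0.15 | 8.1% |

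With no dropout (30 per arm), the change comparison gives 6.2%, 12.7% and 36.3%. More participants do not help: the bias stays the same while the standard error falls.

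**The case against.** **Participants may not know their arm at week 0.** A reader might infer that they do, but no section says when the arm is disclosed. The Procedure paragraph is also not strictly chronological, since it describes the platform and the therapists between platform entry and baseline. This objection stands: the text supports only that participants are already allocated, unblinded, and may know.

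**The schedule figure might settle it.** The legend of Fig 1 lists two baseline timepoints, T1 and T2, before the intervention. The figure is not available here, so a baseline before allocation cannot be excluded. If it shows one, it conflicts with Procedure and Outcome evaluation, and the problem is one of reconciling the text.

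**The bias need not enter in full.** A reader might infer that any shift passes one for one into the estimate. Participants are equally unblinded at later ratings, so the part of a shift that persists cancels in the change score. Only the part that fades biases it. Nor is baseline adjustment made useless: it cuts the bias to r x d. The plan does not specify that adjustment, however.

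**The 28% rests on an assumption.** It belongs to the top of an assumed range, and at 0.1 SD the inflation is trivial. This stands.

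**Randomisation method.** The article says "An independent researcher will conduct participant randomization using the MS Excel randomization function with a 1:1 ratio" and reports a split so far of "e-CBTi: n = 11; trazodone: n = 7". A reader might infer simple, unblocked randomisation and a harmful imbalance. The documents do not support that. Blocking details are commonly left to a full protocol, and 11:7 is compatible with chance (two-sided binomial p = 0.48). Even 35:25 keeps 4 x 35 x 25 / 60^2 = 97.2% of the efficiency of equal arms. Nothing here depends on it.

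**Conclusion.** The concern holds in a limited form. On the available text, the baseline ISI and diary follow allocation in an unblinded trial, and nothing described protects the primary comparison from an arm-dependent shift at week 0. The text does not establish that participants know their arm at that moment, that any shift occurs, or its direction.

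The illustrated type I error of about 5.9% to 28% rests on three assumptions: a shift of 0.1 to 0.5 SD, none of it persisting to the end of treatment, and an unadjusted comparison of change with 22.5 per arm and r = 0.3. If part of the shift persists, or baseline is a covariate, the inflation is smaller. The case for acting is that the bias could not be recognised or removed afterwards, whereas preventing it takes only a change of order and leaves the sample size as it is.

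**What to change.** 1. For all further participants, use this order: consent, MINI, OPTT access, then baseline ISI, demographic survey and baseline diary completed and locked. Only then generate or reveal the allocation.
2. Align Fig 1, Procedure and Outcome evaluation with this order, and state when the arm is disclosed.
3. For those already recruited (18 at the time of writing), report whether the baseline preceded disclosure of the arm. Run a sensitivity analysis excluding participants whose baseline came after it.

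If applied from the time of writing, the new order would cover up to 60 - 18 = 42 participants. It removes the influence of the known arm on the baseline. It does not remove the unblinded self-rating at later visits, which is inherent in the design.

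Cost: a short ethics amendment and slightly more set-up for people who are not finally randomised.
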